## Abstract

**Background:**

Maternal mortality in much of sub-Saharan Africa is very high whereas there has been a steady decline in over the past 60 years in Europe. Perinatal mortality is 12 times higher than maternal mortality accounting for about 7 million neonatal deaths; many of these in sub-Saharan countries. Many of these deaths are preventable. Countries, like Malawi, do not have the resources nor highly trained medical specialists using complex technologies within their healthcare system. Much of the burden falls on healthcare staff other than doctors including non-physician clinicians (NPCs) such as clinical officers, midwives and community health-workers. The aim of this trial is to evaluate a project which is training NPCs as advanced leaders by providing them with skills and knowledge in advanced neonatal and obstetric care. Training that will hopefully be cascaded to their colleagues (other NPCs, midwives, nurses).

**Methods/design:**

This is a cluster randomised controlled trial with the unit of randomisation being the 14 districts of central and northern Malawi (one large district was divided into two giving an overall total of 15). Eight districts will be randomly allocated the intervention. Within these eight districts 50 NPCs will be selected and will be enrolled on the training programme (the intervention). Primary outcome will be maternal and perinatal (defined as until discharge from health facility) mortality. Data will be harvested from all facilities in both intervention and control districts for the lifetime of the project (3–4 years) and comparisons made. In addition a process evaluation using both quantitative and qualitative (e.g. interviews) will be undertaken to evaluate the intervention implementation.

**Discussion:**

Education and training of NPCs is a key to improving healthcare for mothers and babies in countries like Malawi. Some of the challenges faced are discussed as are the potential limitations. It is hoped that the findings from this trial will lead to a sustainable improvement in healthcare and workforce development and training.

**Trial registration:**

ISRCTN63294155

## Background

Maternal mortality and morbidity associated with pregnancy remain major challenges to improving health in Africa. Prior to 2005 it was reported that six hundred thousand women die every year as a result of complications from pregnancy and childbirth
[1]. The World Health Organisation reported in 2008 that there were 358,000 maternal deaths globally and while there have been some improvements since
[2], most of these deaths are preventable. Human resources and the effective service delivery of appropriate sustainable technologies have been identified as key areas that need support if this global inequity in health is to be improved. The Millennium Development Goals 4 and 5 of reducing maternal and perinatal mortality can only be achieved by developing and evaluating innovative transferable and sustainable solutions through collaboration between African and International partnerships.

Maternal mortality in most of sub-Saharan Africa remains obstinately high
[3]. In Malawi, for example, the maternal mortality ratio is 675/100,000 whereas in the UK it is 13/100,000
[3-5]. Whereas there has been a steady decline in maternal mortality in Europe over the past 60 years, in Africa even long periods of stability and increases in health spending have had little effect in many countries
[5]. The UN has set a target for maternal case fatality rate of less than 1%. Many women in rural and urban communities in Africa give birth without any trained assistance for their pregnancy and childbirth as less than 50% of women in low-income countries are attended by skilled health personnel at birth, yet life-threatening complications that require emergency care will arise for around 15%
[6]. Perinatal mortality is 12 times higher than maternal mortality and accounts for seven million deaths: about three million babies are stillborn and four million die in the neonatal period. Much of this loss is preventable
[3,6,7]. The major causes of the almost four million neonatal deaths in low-income countries in or around the first week of life are infection, pre-term birth and asphyxia
[6].

Models of healthcare, which have developed in Europe, based on highly trained medical specialists using complex technology, are unlikely to be a practical way forward or sustainable in sub-Saharan Africa. There is evidence to support a different model of service provision in Africa, whereby the relatively scarce resource of medical obstetric specialists are focused to train and support a service mainly provided by healthcare staff other than doctors, i.e. non-physician clinicians (NPCs) such as assistant medical officers, clinical officers, midwives and outreach community health-workers. In this model, the medically trained specialist obstetricians, mainly operating in large centres and capital cities, can focus their attention on management of difficult clinical cases and on providing support, leadership and training for NPCs. Many women in rural and urban communities in Africa give birth without any trained assistance for their pregnancy and childbirth. In sub-Saharan Africa, due to training and retention difficulties, there are only 5 doctors per 100,000 people
[1] and in Malawi it is even worse with only 2 per 100.000
[8]. Programmes of training for health-workers to provide safe outreach community healthcare are being developed but these need to be systematic, transferable, and able to be scaled up to meet the needs of these women across Africa. A health delivery model of non-physician clinicians (NPCs) with support and supervision of the physician specialist obstetricians would be an affordable and sustainable system for these communities.

Work has been done to assess the efficiency of training NPCs (assistant medical officers, clinical officers and specialist midwives) in the skills of clinical decision-making and surgical intervention
[1,7]. Training skilled attendants to prevent, detect and manage major obstetric complications, including undertaking emergency caesarean surgery in complicated deliveries is arguably the single most important factor in preventing maternal deaths and protecting the human rights of women
[1,7,9,10]. To be effective NPCs need appropriate equipment, drugs and technology essential for managing obstetric complications in rural or deprived communities.

Task shifting from physicians to non-physicians appears to be both safe and effective in countries that have organised and supported the extension of their maternal care in this way
[1,9-14]. Major surveys consistently show that extra training and support can achieve task shifting and improve maternal and foetal mortality and morbidity in the areas where these schemes have been piloted
[9,11,13]. Most of the maternal population in sub-Saharan Africa lives in rural areas and for these women there remains major challenges to effective maternal care. Solutions must include outreach of effective care to this population. In addition to lack of available trained manpower, factors that have been identified as contributing to the higher maternal and perinatal mortality, include poor availability of relatively cheap drugs and simple technologies for managing post-partum haemorrhage (PPH); shortages of immediately available blood; lack of access to senior advice at all times; access to facilities and staff for emergency Caesarean sections; and delays and inadequacies in the safe transport to hospital when complications arise. There can also be a problem recognising complications early enough for effective action, (for example; breech, transverse lie, placenta praevia, pre-eclampsia and anaemia). Early detection of these could be improved with training and simple technologies. It is estimated that 75% of maternal deaths and more than 60% of perinatal deaths are caused by 8 major conditions. For the mother the 5 major killers are post-partum haemorrhage, sepsis, hypertensive disorders of pregnancy, obstructed labour, and unsafe abortion and the 3 major causes of perinatal mortality are low birth-weight, birth asphyxia, and infection
[11,15].

### Rationale/justification for the research project

In Malawi, training and deployment of NPCs can be traced as early as 1875 when [name] started on the job training of Medical Orderlies and Medical Assistants. The Government introduced formal training of Clinical Officers in 1976 and this cadre is a major human resource for health in Malawi as far as clinical services are concerned; performing surgical procedures, giving anaesthetics and providing medical care. NPCs have been established health providers in Malawi for a long time, yet lack a clear career pathway
[16,17]. Currently there is disparity between Malawi’s service coverage figures and maternal and child mortality. For example, coverage for skilled attendance and childbirth is 72% (Malawi DHS 2010) and contraceptive prevalence is 42% and yet maternal and child mortalities are very high. It is hoped that by providing NPCs with advanced leadership and skills training (the intervention) we will have an impact on maternal and perinatal morbidity and mortality) and help to strengthen the position of mid-level providers to expand cost-effective, quality services to under-serviced areas and thereby improve equitable access to care.

## Aims of the study

### Broad aims

The main aims of this study are to evaluate the impact on health outcomes (e.g. maternal and perinatal morbidity and mortality) of the intervention comparing intervention districts with control districts, and how well (or poorly) the intervention was implemented including how acceptable it was to all stakeholders.

### Specific aims

To explore changes in maternal and perinatal mortality outcomes comparing intervention districts with controls.

The primary outcome is perinatal mortality (pragmatically defined in this study as fresh stillbirths and neonatal deaths before discharge from the health care facility)

Secondary outcomes include:

• Maternal death rates (case specific);

• Recorded data (e.g. still births, Post-Partum Haemorrhage, Caesarean Section, Eclampsia, Sepsis, Neonatal resuscitation);

• Availability of resources (e.g. are drugs/blood available);

• Use of available resources (e.g. are drugs being used).

Alongside this we plan to carry out a process evaluation of the implementation of the intervention to inform future implementation of interventions like these or to develop it further for the future. The process evaluation will include outcomes which will explore how or why the intervention was either effective or not effective. Including:

• What was done and by whom;

• Challenges faced;

Acceptability;

• Sustainability.

Process evaluations particularly help researchers understand the causal pathways by which complex interventions might work and sometimes to interpret equivocal results. The shift towards greater evidence-based-practice means there is a greater need to know why an intervention works and, if it does not, why not. Process evaluation can facilitate this understanding and should be incorporated into the evaluation of health promoting interventions/programmes
[18].

## Methods

### Design

The study is a cluster randomised controlled trial.

### Study place

The study will be conducted in districts within the central and northern regions of Malawi. There are a total of 14 districts in these regions which will be randomised to either intervention or control (Dedza, Dowa, Kasungu, Lilongwe, Mchinji, Nkhotakota, Ntcheu, Ntchisi, Salima, Chitipa, Karonga, Mzimba, Nkhata Bay, and Rumphi). A pragmatic decision was made that as Lilongwe is such a large district it would be divided into two with one half randomised to intervention and the other to control making a total of 15 districts. Stratified randomisation of the districts, to ensure the two groups are comparable will be carried out by a statistician at the University of Warwick, UK who will then inform the study team of the outcome. There will be 8 intervention districts and 7 controls. Control districts will be offered the intervention at the end of the trial as part of a randomised waiting-list design.

### Research team

The primary data collection team will consist of a research assistant based out of the College of Medicine (in Blantyre, Malawi) and a selection of trained clinical officers from each of the intervention districts (1 or 2 from each district). These clinical officers will be provided with basic training in research methods and full training collecting the quantitative data from their own and an adjacent control district by the research team at the University of Warwick. The Malawi team will be supported locally by colleagues within the Ministry of Health and the College of Medicine and by visits from the UK team; as well as regular electronic/mobile contact. The College of Medicine research assistant will visit all districts and carry out checks on data recording accuracy as well as providing a point of contact and support.

### Study population

Within the eight intervention districts approximately 50 NPCs will receive advanced leadership and skills training (the intervention). In each district randomised to the intervention between 3 and 8 NPCs (the number depends on size of district but a minimum is 3 in one district with the overall total not exceeding 50). The research assistants will invite the ‘trained’ NPCs to be involved in the evaluation. Their involvement will be related to the process evaluation and will include interviews and recording their project based activities. District medical and nursing officers in the intervention districts will be invited to be interviewed about the districts involvement in the intervention and at follow-ups how the intervention has worked/fitted in to the hospital routine. As part of the intervention the trained NPCs are expected to cascade the training they have received to others within their districts (e.g. other NPCs or midwives). The research assistant will identify a number of these people from the NPC’s records and they will be approached and interviewed about the training they received and how they have been able or indeed unable to implement what they have been taught. All participants will be provided with information about the study and asked to provide written informed consent.

### Study period

Anticipated start date is 01/11/2011 with an anticipated end date of 28/02/2014

### Sample size

The primary sample for the RCT is the fifteen districts, the health facilities within them and 50 participating NPCs from the 8 intervention districts.

#### ***Justification of sample size***

##### Power calculation

The project’s primary outcome measure is the proportion of live-born infants who died in the hospital or health facility in the early neonatal period, i-e, from birth to the day of discharge from facility. Other outcome measures of interest considered are the comparisons of proportions of fresh stillbirths. We computed a sample size for proportion in an unmatched study with 80% power, a one sided alpha of 0.05, and an Inter Class Correlation of 0.0025. The current neonatal mortality rate in Malawi: is 30 per 1000 live births
[19] and assuming a minimum number of clusters of 14 in our sampled districts, the study was powered to detect a 20% difference between the two birth cohorts (intervention and control) in the proportion of live-born neonates delivered by NPCs or staff trained by them) surviving to hospital discharge.

With the allocation of 7 districts per arm with an estimated 700 births per NPC (or staff trained by them), 1028 births per study arm per district would provide sufficient power for a total of 2056 neonates per district. That is, a decline from 30 per 1000 live births to 24 per 1000 live births, rate ratio 0.20.

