## Discussion

Education and training for Non-Physician Clinicians (NPCs) is the key to improving healthcare for mothers and babies in Sub-Saharan Africa where there are few medical doctors. The primary objective of the ETATMBA project is to develop, implement and evaluate a programme of locally-based clinical service improvement including clinical guidelines, structured education, leadership training and workforce development, which will be linked to specialist support; this trial aims to evaluate the impact of ETATMBA in Malawi.

There are challenges to running a trial in Malawi, a resource sparse country. The trial/project covers two thirds of the country and travel and communication links can be difficult. A major challenge will be data collection. In pilot work carried out at the early stages of the project it was noted that there is very good record keeping in hospitals and health centres with summary data regularly sent to the district hospitals. Thus each district has a fairly comprehensive archive of data (on paper). This data are entered onto electronic databases for national records. However, these databases are far from reliable and up to date. The ETATMBA intervention aims to encourage trainees to think about innovative ways of dealing with the issues/problems they face. The research team also have to be innovative in our approaches to gather data across Malawi; the training of local data collectors supported by the team from a distance is how we plan to achieve this.

Along with the challenges there are also limitations. Our primary outcomes of maternal and perinatal mortality (within medical facilities) in a country like Malawi are influenced by many factors other than our intervention. Randomisation addresses some of the confounding factors but there is a plethora of local or NGO delivered programmes which come and go in one district but not in another. Thus it may be difficult to attribute any changes to our intervention. However, pragmatically, the randomised nature of the trial does mean this should be minimised.

A strong driver for the overall ETATMBA project was to develop and deliver a programme which was sustainable after the project ended supported by the Ministry of Health and the University of Malawi. The evaluation trial will hopefully provide evidence to ensure a sustained effort in the fight to reduce maternal and perinatal mortality in countries like Malawi.

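### Three incompatible primary outcomes are stated, and the one used for the sample size is not the one named in the specific aims

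*Protocol article*

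**What the plan says.** Four places in the protocol article state what is primary.

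- Abstract, Methods/design: "Primary outcome will be maternal and perinatal (defined as until discharge from health facility) mortality".
- Discussion, in the plural: "Our primary outcomes of maternal and perinatal mortality (within medical facilities".
- Specific aims: perinatal mortality alone, meaning "fresh stillbirths and neonatal deaths before discharge from the health care facility". Maternal death heads the list of secondary outcomes.
- Power calculation: the "primary outcome measure is the proportion of live-born infants who died in the hospital or health facility in the early neonatal period". Fresh stillbirth is set apart: "Other outcome measures of interest considered are the comparisons of proportions of fresh stillbirths".

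The sample size is worked out for the last of these, as a fall from 30 to 24 per 1000 live births with "80% power, a one sided alpha of 0.05, and an Inter Class Correlation of 0.0025". The Data analysis section has a heading for primary outcomes and describes a quarterly interrupted time series, but does not say which outcome it analyses.

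**The concern.** The definitions disagree on two components: whether maternal death is primary, and whether fresh stillbirth is part of the primary outcome. They also imply different denominators, because a measure that counts stillbirths needs all births, whereas the Power calculation uses live births only.

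A reader of the final report could not tell from this article which comparison was meant to be confirmatory. If the three results differ, the article supports any of them as the headline. The sample size offers no assurance for the composite in the aims or for maternal mortality, since neither is calculated.

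The powered definition has a further weakness. Whether a baby is live-born is decided after randomisation and may be affected by the training. Module 1 covers birth asphyxia, and neonatal resuscitation is among the recorded outcomes. If better care at birth produces live births that would otherwise have been fresh stillbirths, those infants join the denominator, and those who die join the numerator.

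**Working it through.** **1. The sections side by side**

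| Section | Maternal death | Fresh stillbirth | Denominator |
|---|---|---|---|
| Abstract; Discussion | primary | not stated (perinatal) | not stated |
| Specific aims | secondary | in the primary | not stated; all births implied |
| Power calculation | not mentioned | outside the primary | live births |

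No single outcome satisfies all three rows.

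**2. Which outcome the sample size belongs to**

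The planning rates, 30 and 24 per 1000, are per live birth, so the calculation belongs to the third row. The stated 1028 births per district does not reproduce for 30 against 24. The individually randomised requirement is 9,023 per arm, and 9,023 × 0.0025 = 22.6, so at least 23 districts per arm would be needed at the stated ICC. That is a separate matter and nothing below depends on it.

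The calculation cannot simply be carried over to the composite. The article gives no fresh stillbirth rate. Assuming 10, 20 or 30 fresh stillbirths per 1000 births and 3% deaths among live births, the composite rate is:

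- 10 + 0.03 × 990 = 39.7 per 1000 births
- 20 + 0.03 × 980 = 49.4 per 1000 births
- 30 + 0.03 × 970 = 59.1 per 1000 births

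These are 1.3 to 2.0 times the rate used for planning.

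**3. Reclassification**

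Let L be live births, D deaths among them, x the would-be fresh stillbirths that become live births, and d their death risk before discharge. The live-born rate becomes (D + xd)/(L + x). This exceeds D/L exactly when d > D/L, here 3%. Total perinatal deaths fall by x(1 − d), so they fall whenever any of these infants survive.

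Illustration with assumed inputs: 20 fresh stillbirths per 1000 births, 30% of them revived (x = 6), d = 50%. Then L = 980 and D = 29.4.

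- Live-born rate: 30.0 before; (29.4 + 3)/986 = 32.9 per 1000 after; ratio 1.10.
- Perinatal rate: 49.4 before; 14 + 32.4 = 46.4 per 1000 births after; ratio 0.94.

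Over fresh stillbirth rates of 10 to 30 per 1000, 20 to 50% revived and d of 30 to 70%, the live-born ratio is 1.02 to 1.34 and the perinatal ratio 0.82 to 0.985.

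**4. The same, with the design effect on other infants**

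If deaths among the other live-born infants also fall by 20%, D becomes 23.52. The live-born rate is then (23.52 + 3)/986 = 26.9 per 1000, ratio 0.90. The perinatal rate is 14 + 26.52 = 40.5 per 1000 births, ratio 0.82.

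Over a grid of 36 combinations (fresh stillbirth 10, 15, 20, 30 per 1000; revived 20, 30, 50%; d 30, 50, 70%), the live-born ratio runs from 0.82 to 1.14 and exceeds 1 in 4 combinations. The perinatal ratio stays between 0.72 and 0.87.

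To cancel the 20% reduction fully, x = 0.2 × 0.03 × L/(d − 0.03). With L = 980 this is 5.88/0.27 = 21.8 per 1000 births at d = 30% and 5.88/0.67 = 8.8 at d = 70%.

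**The case against.** **The analysis plan may settle the choice.** It may, and its absence here is no fault. But the article does more than omit detail: its sections contradict one another, and an analysis plan could only resolve that by overruling some of them. A reader might infer that the team means to pick the favourable result. Nothing in the documents says so; the point is only that this text does not prevent it.

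**Reversal is an edge case.** This largely stands. The training also covers low birth weight, infection and asphyxia in infants already live-born. In the illustration, break-even needs the other deaths to fall to 0.03 × 986 − 3 = 26.58, and 1 − 26.58/29.4 = 9.6%, well under the planned 20%. The stillbirth rate, share revived and death risk are all assumptions, and the article never states that resuscitation is taught; that is inferred. Bias towards apparent harm is therefore not an established fact.

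**Other inferences that the documents do not support.**

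- *Knowledge and satisfaction scores are primary outcomes.* They appear under that heading in Data analysis, but the Quantitative data collection section assigns knowledge scores and training feedback to the process evaluation, and scores are to be presented descriptively.
- *Maternal mortality has a known, very low power.* Using 7 × 1028 = 7,196 births per arm takes the stated requirement for the births to be observed. About 50 NPCs × 700 births suggests 35,000 in the intervention arm, and no ICC for maternal death is given.
- *The false positive rate is that of two or three independent tests.* Live-born death is a component of the composite, so the outcomes overlap and that figure does not apply.

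**Conclusion.** The contradiction holds on the text alone and needs no assumption: three primary outcomes, no ranking, and a sample size for a definition that differs from the specific aims. It bears on the trial's main conclusion and should be corrected.

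The reclassification argument is a conditional support for choosing the composite. The direction of the effect follows from algebra once revived infants die at more than 3%. Its size rests on assumed rates: a live-born ratio of 1.02 to 1.34 if nothing else changes, and 0.82 to 1.14 if other deaths fall by 20%. Dilution of the planned effect is the usual result and reversal the exception. A reader might infer that a beneficial programme would look harmful; the documents support only that it could, under some of these rates.

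**What to change.** Make the Specific aims composite the single primary outcome everywhere: fresh stillbirths plus in-facility neonatal deaths up to discharge, divided by live births plus fresh stillbirths. In the Abstract, Power calculation and Discussion, make live-born neonatal death, fresh stillbirth and maternal death secondary, and refer to the composite by name in Data analysis.

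Restate the power calculation for the composite. Take the fresh stillbirth rate from the 12-month baseline registers, or give it as an explicit assumption with a range. State the ICC assumed for the composite as well. The number of districts is fixed, so the restated calculation can report the power or detectable difference available.

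The cost is a few wording changes and one recalculation. Fresh stillbirths and neonatal deaths are already planned outcomes, so no new outcome is needed. The recalculation cannot be done from the article as it stands, because the fresh stillbirth rate is missing.

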### ***Data collection***

#### ***Quantitative data collection***

Primary data will be extracted from the maternity log (Malawi Ministry of Health Maternity Register, Version 2 (July 2008)) at the district hospital and rural hospitals in each district by the research assistants monitored by the local and UK team. Other facilities within the district (e.g. health Centres) also complete the same maternity log book from which summary data is returned to the district hospital on a monthly basis. These data will also be gathered by the researchers and the combined data will make up a complete picture of the districts. Data will be collected at three points in time. Baseline data will be collected on cases (from the maternity logs and summary logs) for the 12 months prior to the date the training was delivered with two follow-ups at 12 monthly intervals. A paper case report form (CRF) will be produced to facilitate data collection. Data will then be transferred to an MS Excel spread sheet for transfer to the study database.

It is planned that our primary data will be that collected at source (i.e. each district). However, for the purposes of comparisons national data from national databases will also be sourced via our collaboration with the Malawian Ministry of Health for the same time periods.

Within the intervention districts at the three time points (baseline, 12 and 24 months) the research assistants will approach the consenting NPCs (primarily to interview them, described below) but also to gather information about project related activities (e.g. who they have trained, when they did this, how many training session done, etc.).

For process evaluation purposes training registers, adherence to training procedures (during the project period), knowledge scores and training feedback will also be collected and collated from the intervention team. No identifiable data will be recorded

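### The power calculation's baseline rate and 20% effect belong to different deaths and births from those the trial will analyse

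*Protocol article*

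**What the plan says.** The Power calculation section of the protocol article defines its outcome as death of a live-born infant in the facility up to discharge. The control rate that follows is a country-level one: "The current neonatal mortality rate in Malawi: is 30 per 1000 live births". The effect is "a decline from 30 per 1000 live births to 24 per 1000 live births, rate ratio 0.20", and it is set "in the proportion of live-born neonates delivered by NPCs or staff trained by them". The births are counted on the same basis: "With the allocation of 7 districts per arm with an estimated 700 births per NPC (or staff trained by them"). The error rates and clustering are "80% power, a one sided alpha of 0.05, and an Inter Class Correlation of 0.0025".

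Other sections describe a different set of births. The abstract says "Data will be harvested from all facilities in both intervention and control districts". Under Quantitative data collection, hospital maternity logs are joined with monthly summaries from the other facilities, and "the combined data will make up a complete picture of the districts". The Data analysis section compares intervention with control districts on the district maternity register data, with no restriction by birth attendant. The Specific aims define the primary outcome as perinatal mortality, counting fresh stillbirths together with neonatal deaths before discharge.

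**The concern.** Two planning inputs do not match what will be analysed.

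- **Deaths.** In its usual meaning, a national neonatal mortality rate covers all neonatal deaths wherever they occur. The trial's outcome stops at discharge and is seen only in facilities. Under the Specific aims it also includes fresh stillbirths, which a rate of deaths among live births leaves out. Nothing in the article converts one rate into the other.
- **Births.** The 20% reduction is assumed for births attended by NPCs or by staff they trained, but the comparison uses every facility birth in the district. About 50 NPCs are trained, 3 to 8 per intervention district (Study population), and they are expected to pass the training on. Any register birth that this training does not reach pulls the district-level effect below 20%. No allowance is made for that.

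A reader who takes the power statement at face value will misjudge what the trial can detect, and may read a null result as evidence that the training does not work.

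**Working it through.** **Inputs from the Power calculation section:** control rate 30 per 1000, intervention rate 24 per 1000, 7 districts per arm, 1028 births per district, ICC 0.0025, one-sided 5% (z = 1.645), 80% power. **Assumed, because the article gives neither:** the facility rate of the analysed outcome (10 to 50 per 1000) and the share of births attended by trained or cascade-trained staff (100% to 25%).

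**The plan's own figure.** With individual randomisation, n per arm = 6.183 × (0.0291 + 0.023424) / 0.006² ≈ 9,020. At ICC 0.0025 the clusters needed per arm must exceed n × ICC ≈ 22.6, so no cluster size reaches 80% with 7 per arm and 1028 is not reproduced. Of the variants tried, only two-sided 5%, ICC 0.00025 and 14 clusters per arm returned it: 11,455 × 0.99975 / (14 − 11,455 × 0.00025) = 1028.4. That is a separate defect. It is used here only to show the effect of the mismatch from an 80% starting point.

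**Power with the stated inputs.** Design effect = 1 + 1027 × 0.0025 = 3.5675. Effective births per arm = 7 × 1028 / 3.5675 = 2,017. Power = Φ{ |p1 − p2| / √[(p1(1 − p1) + p2(1 − p2)) / 2,017] − 1.645 }. At 30 v 24 per 1000 this is Φ(1.176 − 1.645) = 32%.

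**Changing the baseline rate, 20% reduction kept.** The ICC can be held at 0.0025. Alternatively, the between-district coefficient of variation can be held at √(0.0025 × 0.97 / 0.03) = 0.284, so that ICC = 0.284² × p / (1 − p).

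| Rate per 1000 (assumed, except 30) | Power, ICC held | Power, CV held | Power, input set that yields 1028 |
|---|---|---|---|
| 10 | 17% | 24% | 36% |
| 20 | 25% | 29% | 62% |
| 30 | 32% | 32% | 80% |
| 40 | 39% | 34% | 90% |
| 50 | 46% | 35% | 95% |

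**Diluting the effect, baseline 30 per 1000.** District-level reduction = 20% × coverage, assuming no effect on other births. At 50% coverage, p2 = 0.030 × 0.90 = 0.027 and power = Φ(0.573 − 1.645) = 14%.

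| Coverage (assumed) | District reduction | Power, stated inputs | Power, input set that yields 1028 |
|---|---|---|---|
| 100% | 20% | 32% | 80% |
| 75% | 15% | 22% | 54.5% |
| 50% | 10% | 14% | 28% |
| 25% | 5% | 9% | 10% |

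**Larger districts.** If the article's 700 births per NPC are applied to 50 NPCs over 8 districts (4,375 per district), effective births per arm rise only to 7 × 4,375 / (1 + 4,374 × 0.0025) ≈ 2,566. Power for reductions of 20%, 15%, 10% and 5% is then about 37%, 25%, 16% and 9%.

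**The case against.** - **Direction of the rate error.** A reader might infer that 30 per 1000 must be too high, since deaths before discharge are a subset of neonatal deaths. That holds only for the same births and for the live-born definition. The Specific aims add fresh stillbirths, and facility births, which may include referred complicated cases, are not all births in Malawi. The rate could be higher and power with it. This objection stands, so the range has to run both ways.
- **Size of the rate effect.** Holding the ICC while the rate falls to 10 per 1000 implies that the between-district CV rises from 0.284 to 0.497, which nothing in the article supports. With the CV held, the loss from 30 to 10 per 1000 is about 8 points. This also stands.
- **Coverage.** The article gives no share of births missed by the training, and cascading is part of the intervention. The size of the dilution is therefore unknown. Its direction is not: if any register births gain less than the full effect, the district effect is below 20%.
- **Loss of randomisation.** A reader might infer that births will be selected by attendant, which would break the randomised comparison. The article does not support this. Its data collection and analysis sections use register data from all facilities and compare districts. The wording on NPC births appears only in the power calculation, and NPCs are an established cadre nationally.
- **Design features left out.** These figures ignore the 12-month baseline and the quarterly series, which may change precision. They do not repair a mismatch of outcome and population.

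**Conclusion.** The point holds as a mismatch of planning inputs. The 30 per 1000 is not the rate of the outcome to be analysed, and the documents do not show whether it is too high or too low. Over assumed rates of 10 to 50 per 1000, power with the stated inputs runs from 17% to 46%, or about 24% to 35% with the CV held. The undiluted 20% effect can only flatter the power: at assumed coverage of 75%, 50% or 25%, with no benefit to other births, power falls from 32% to 22%, 14% or 9%. The fall is not an artefact of the low start, since the input set that yields 1028 drops from 80% to 28% at 50% coverage. That the stated inputs give 32% rather than 80% even at 30 per 1000 is a separate error and is not attributed to this mismatch.

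The conclusion rests on the usual meaning of a neonatal mortality rate (the cited source was not available), on the two assumed ranges, and on a normal approximation for 7 districts per arm.

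**What to change.** In the Power calculation section:

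1. Replace 30 per 1000 by the rate of the chosen primary outcome, with its matching denominator, from the trial's own 12-month baseline registers. Until those data are in, give a range on both sides of 30.
2. State that the target effect applies at district level to all facility births, as 20% times an assumed coverage, and give the basis for that coverage.
3. Restate the resulting power over both ranges, and say whether the ICC or the between-district CV is held as the rate changes.

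The cost is a recalculation from data already being collected. The baseline registers are gathered after randomisation and the clusters are all the districts of the two regions, so this corrects the description of power rather than the number of clusters. The stated power will probably be less favourable.
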